### Control group

Cognitive behavioral therapy is a widely recognized non-pharmacological intervention for PSD, focusing on modifying negative thought patterns and maladaptive behaviors that contribute to emotional emotional distress and impaired functioning. CBT training consists of a 3-h group-based health education seminar delivered at baseline to provide psychoeducation on stroke and emotional well-being, followed by a 2-week structured course comprising five sessions per week. Each CBT session lasts approximately 30 min and is conducted under the supervision of a qualified therapist with over 5 years of professional experience in psychotherapy. Interventions include:

Disease education: Introduce the causes, clinical manifestations, and treatment methods of PSD formation to patients, enabling them to gain a basic understanding of the disease and guiding them to actively cooperate with treatment.Establishing trust: Proactively caring for patients, harmonizing doctor-patient relationships, enhancing doctor-patient trust, creating a warm, relaxed, and confident emotional environment for patients, and enhancing their sense of security.Identifying negative emotions: comprehensively understanding the patient’s emotions, mentality, exploring their negative factors and automatic thoughts.Changing Negative Cognition: Actively Identifying and Improving Potential Functional Impairment.

### Outcomes measures

#### General information collection

General information data include age, gender, education level, occupation, alcohol consumption and Smoking status.

#### Primary outcomes

The primary outcome measure for evaluating the severity of post-stroke depression is the 17-item Hamilton Depression Rating Scale (HAMD-17). This scale is a clinician-administered tool that quantitatively assesses depressive symptoms across multiple domains, including mood, anxiety, physical complaints, and psychomotor changes. HAMD-17 is particularly suitable for PSD as it captures somatic symptoms often present in stroke patients. A score >7 and ≤ 24 will be used to confirm mild to moderate depression, ensuring appropriate inclusion of participants in the study. Assessments will be conducted at baseline, midpoint (1 weeks), and at the end of the intervention (2 weeks) to evaluate changes in depressive symptoms over time. All evaluations will be performed by trained and blinded assessors to minimize measurement bias and maintain the integrity of the study.

In this study, rs-fMRI will serve as the second primary outcome measure to investigate neural mechanisms underlying post-stroke depression and its treatment effects. The imaging data were acquired using a United Imaging uMR780 3.0 T MRI system equipped with a 32-channel rigid head coil. Participants wore noise-canceling headphones, kept their eyes closed, remained awake, and minimized thoughts. The T1-weighted (T1W1) structural imaging parameters were as follows: TR = 7.2 ms, TE = 3.1 ms, flip angle = 10°, field of view (FOV) = 256 mm × 256 mm, slice thickness = 1 mm, and 192 slices. fMRI parameters included: TR = 2000 ms, TE = 30 ms, flip angle = 90°, FOV = 224 mm × 224 mm, matrix size = 64 × 64, and 33 slices. The voxel size was 3.5 mm × 3.5 mm × 3.5 mm, with 240 time points collected in each scan session, lasting 8 min per session.

Resting-state fMRI data were preprocessed using SPM12 software. The preprocessing steps included slice timing correction to account for temporal offsets in slice acquisition, realignment to correct for head motion, and coregistration of the functional images to the corresponding T1-weighted structural images. Segmentation of the T1 images was performed to generate normalization parameters, which were applied to transform the functional images into MNI space. Finally, spatial smoothing was conducted using a 6-mm FWHM Gaussian kernel to enhance the signal-to-noise ratio.

Regional Homogeneity (ReHo) is a data-driven method used in rs-fMRI to assess the synchronicity of spontaneous neural activity (23). It quantifies the temporal consistency of the BOLD signal within a given voxel and its 26 nearest neighbors, typically using Kendall’s coefficient of concordance (KCC). ReHo reflects the synchrony of local BOLD signal time series, rather than the signal intensity itself. This metric is widely employed to evaluate the functional integrity of local brain regions and their role in neural network dynamics, providing insights into regional brain activity and connectivity.

Amplitude of Low Frequency Fluctuations (ALFF) is widely used in fMRI to assess the strength of spontaneous brain activity in the resting state. By examining low-frequency fluctuations in the BOLD signal, typically within the 0.01–0.08 Hz range, ALFF provides insights into neural activity across different brain regions. A study has shown that severe depression patients exhibit significantly reduced ALFF values in the bilateral frontal poles after antidepressant treatment (24). There are also research findings, that increased ALFF values in the right inferior frontal gyrus and anterior insula have been associated with insomnia symptoms in depression, but not with anxiety or depressive symptom severity (25). These findings highlight ALFF’s utility in identifying regions with altered neural dynamics and their potential relationships to specific clinical features, offering valuable perspectives on the neural mechanisms underlying psychiatric disorders.

Functional Connectivity (FC) reflects the interdependence of neural signals across brain regions, providing insights into spontaneous neural activity and the coordination of brain networks during rest or task performance (26, 27). In fMRI, FC is assessed by measuring the temporal correlation of BOLD signal time series, either between predefined regions of interest (ROIs) or across the entire brain, to explore intrinsic neural networks and their dynamic interactions. Research indicates that FC between the anterior insula and the superior frontal regions is significantly higher in patients with PSD. This finding highlights altered neural network interactions that may underlie depressive symptoms in PSD.

Independent Component Analysis (ICA) will be performed using the Group ICA of fMRI Toolbox (GIFT, version 4.0, http://icatb.sourceforge.net) to decompose rs-fMRI data into independent components (ICs), allowing for the identification of functional networks within the brain. ICA is a data-driven technique that separates the observed fMRI signal into statistically independent sources, enabling the identification of distinct brain networks based on their temporal correlations.

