**Methods and analysis:**

This study is a non-inferiority randomized controlled trial (RCT). One hundred and twenty-eight participants with PSD will be randomly assigned (1:1) to the intervention group (Tuina + rTMS treatment) and the control group (cognitive behavior treatment). The primary efficacy outcome is the change from baseline to week 2 in Hamilton Depression Rating Scale (HAMD) and Functional Magnetic Resonance Imaging (fMRI). Secondary efficacy outcomes include other assessments of the Mini-Mental State Examination (MMSE), The modified Barthel index (MBI), The National Institutes of Health Stroke Scale(NIHSS), inflammatory factor (IL-6, IL – 17, TNF-*α*, IFN-*γ*, IL-4, IL-10), and Functional near-infrared spectroscopy (fNIRS). Efficacy and scale assessments will be conducted at 1 month and 3 months after the completion of treatment.

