### Sample size calculation

The sample size for this study was calculated based on data from a previous clinical trial (20), in which the HAMD score was 9.90 ± 4.61 in the Tuina therapy group and 13.24 ± 4.36 in the conventional rehabilitation group. The combined standard deviation (*σ*) was 4.49. To detect a difference between group means (*Δ* = 2.5) with a statistical power of 80% (*β* = 0.2, corresponding to Zβ = 0.84) and a significance level of 0.05 (*α* = 0.05, corresponding to Zα/2 = 1.96), the required sample size per group was calculated using the following formula, with calculations performed in G*Power software to ensure adequate statistical power:

$$n=\frac{{\left(Z_{\alpha /2}+Z_{\beta }\right)}^{2}\cdot 2\sigma^{2}}{\Delta^{2}}$$

Thus, each group requires approximately 51 participants. Considering a 20% dropout rate, the adjusted sample size is 64. Therefore, a total of 64 participants per group will be required, resulting in a total sample size of 128 participants.

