#### Statistical analysis of functional magnetic resonance imaging

In this study, fMRI data will undergo preprocessing using SPM12, including slice-timing correction, head motion correction, spatial normalization to the Montreal Neurological Institute (MNI) space, and spatial smoothing with a 6-mm Gaussian kernel. Functional brain networks will be constructed using both seed-based functional connectivity and ICA. For seed-based connectivity, regions of interest (ROIs) will be defined using the Automated Anatomical Labeling (AAL) atlas, and the mean BOLD signal from each ROI will be correlated to generate a connectivity matrix. Group ICA will be conducted using the GIFT software, decomposing the BOLD data into spatially independent components (ICs) that will be matched to canonical brain networks such as the default mode network (DMN), salience network (SN), and frontoparietal network (FPN). Additionally, graph-theoretical metrics, including degree centrality, clustering coefficient, and small-worldness, will be calculated to assess network efficiency and integration. Statistical analyses will involve comparing connectivity strength, network properties, and regional activations between groups using paired or independent t-tests, with corrections for multiple comparisons. Correlations between connectivity measures and clinical outcomes, such as HAMD scores, will be examined using Pearson or Spearman correlation coefficients. This comprehensive approach ensures robust exploration of functional brain networks and their clinical relevance.

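### Two primary outcomes are named, HAMD-17 and rs-fMRI, but the second has no defined variable, no rule links the two, and the sample size covers HAMD alone

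*Protocol article*

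**What the plan says.** The abstract (Methods and analysis) states: "The primary efficacy outcome is the change from baseline to week 2 in Hamilton Depression Rating Scale (HAMD) and Functional Magnetic Resonance Imaging (fMRI". The Primary outcomes section gives HAMD-17 as the measure of depression severity, then says that "rs-fMRI will serve as the second primary outcome measure", and describes its purpose as the study of neural mechanisms and treatment effects.

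No metric, region or network is designated. What the article describes is:

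- **In the outcome text:** regional homogeneity ("Regional Homogeneity (ReHo) is a data-driven method used in rs-fMRI"), low-frequency amplitude ("Amplitude of Low Frequency Fluctuations (ALFF) is widely used in fMRI"), functional connectivity and independent component analysis.
- **In the first fMRI analysis section:** "Functional brain networks will be constructed using both seed-based functional connectivity and ICA", and also "graph-theoretical metrics, including degree centrality, clustering coefficient, and small-worldness, will be calculated". The comparison is worded broadly: "Statistical analyses will involve comparing connectivity strength, network properties, and regional activations between groups".

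On error control, the first fMRI analysis section plans corrections for multiple comparisons without naming a method. The second, which uses network-based statistics, applies a false discovery rate between local networks. The section on scales sets a two-tailed 0.05 level. No section relates the HAMD test to the fMRI tests.

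The Sample size calculation uses HAMD figures only and ends: "Thus, each group requires approximately 51 participants", or 64 per group after allowance for dropout.

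**The concern.** A primary outcome should be one variable whose test can succeed or fail. A change in fMRI cannot do that until someone chooses the metric, the location and the direction that counts as benefit. The article's background does not settle direction: the Primary outcomes section cites higher connectivity between insula and frontal regions in post-stroke depression, while the Discussion cites reduced default-mode connectivity that correlates with anxiety and depression scores.

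The two primaries also have no stated relation, and each possible relation has a cost. Under an either-or rule the trial has more than one route to a positive primary result, so its error rate exceeds 5%. Under a both-required rule the 80% in the sample size section is not the power of the trial. In practice, a significant region in one imaging metric could be presented as a positive primary efficacy result even if HAMD showed nothing.

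**Working it through.** **1. Reproduce the plan's figure.** Inputs from the Sample size calculation: SD 4.49, difference 2.5, Z values 1.96 and 0.84, dropout 20%.

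- n = (1.96 + 0.84)² × 2 × 4.49² / 2.5² = 50.6, so 51 per group.
- 51 / (1 − 0.20) = 63.75, so 64 per group and 128 in total.

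The stated figures reproduce. Every input is a HAMD figure; no fMRI quantity enters.

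**2. If either primary suffices.** Assume one fMRI test and one HAMD test, each at 0.05, independent, with no true effect on either:

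- 1 − (1 − 0.05)² = 0.0975, or 9.75%.
- Whatever the dependence, the bound for two tests is 0.05 + 0.05 = 10%. Positive correlation lowers the figure.
- If several fMRI families each counted as a route to success, the rate would be higher.

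**3. If both primaries must succeed.** No split of alpha is needed, but joint power cannot exceed the lower of the two powers. The documents give no fMRI power, so a range is assumed, with independence. HAMD power at 51 per group is 0.803 by the plan's normal approximation.

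| Assumed fMRI power | Joint power, 51 evaluable per group |
|---|---|
| 50% | 0.803 × 0.50 = 40% |
| 80% | 0.803 × 0.80 = 64% |
| 90% | 0.803 × 0.90 = 72% |

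**4. If alpha is split equally (0.025 each, two-sided).** HAMD power from a two-sample t-test with noncentrality 2.5 / (4.49 × √(2/n)), which is 2.81 at n = 51 and 3.15 at n = 64:

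| Evaluable per group | Alpha 0.05 | Alpha 0.025 |
|---|---|---|
| 51 (full 20% dropout) | 79.5% | 70.4% |
| 64 (no dropout) | 88% | 81% |

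**5. If HAMD is the sole primary, or comes first in a fixed sequence.** HAMD keeps the full 0.05, and the calculation in step 1 applies as it stands.

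**The case against.** The strongest reply is that only a condensed article is available. Alpha allocation, testing order and correction across imaging families are commonly left to an analysis plan or full protocol, and their absence here would not be a finding. That stands for the detailed procedures. It does not cover the choice of primary variable, or whether success means both or either. Those belong in the protocol, and the article does not leave them open by silence: it names two primaries, one of them undefined.

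Several stronger readings are tempting, but the text does not support them:

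- **That there is no control of multiplicity at all.** Both fMRI analysis sections plan corrections. What is missing is a link between HAMD and fMRI. Whether the first section's correction runs within or across metric families is not stated.
- **That every imaging metric is tested at 0.05.** The first fMRI section gives no level. The 0.05 in the second follows its false discovery rate statement and concerns networks. Regional homogeneity and low-frequency amplitude are not named in the statistical sections.
- **That the graph metrics are declared primary.** They appear only in the analysis section.
- **That the error rate is 23% or 26%.** HAMD plus four fMRI families gives 1 − 0.95⁵ = 22.6%, and plus five gives 1 − 0.95⁶ = 26.5%. Both depend on how families are counted, on independence among metrics from the same signal, on an either-or rule and on no correction across families. None of these is in the article.
- **That splitting alpha necessarily cuts HAMD power to 70%.** That holds only if the full 20% drop out.

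**Conclusion.** The point stands in this form: two primary outcomes are declared, the second is a modality without a designated variable, no rule connects them, and the sample size serves HAMD alone. This is a primary outcome that is badly fixed, not detail deferred to another document.

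The size depends on a rule that the article does not give. An either-or rule raises the error rate; a both-required rule costs power instead. The two harms are alternatives and do not occur together. The 9.75% assumes a single fMRI test and independence. The joint-power range rests on assumed fMRI power and independence. The loss is framed at the planned 51 per group: with all 64 evaluable and HAMD power of 88%, joint power could still reach 80%, but only if fMRI power were at least 0.80 / 0.88 = 91%. The HAMD sample size arithmetic itself is correct.

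This should be settled before analysis because it decides what counts as a positive trial.

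**What to change.** Make the week-2 HAMD-17 comparison the sole primary outcome at two-sided 0.05. Reclassify all rs-fMRI measures as secondary or mechanistic, outside the efficacy claim, and keep the corrections already planned within imaging. This matches both the sample size calculation and the mechanistic purpose that the article gives for fMRI.

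If fMRI must keep a ranked role, name one fMRI variable (metric, region or network, and direction) and test it only after HAMD succeeds, in a fixed sequence. HAMD then still keeps the full 0.05.

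Either way, 128 participants and the data collection are unchanged. The work is in the wording of the abstract, the Primary outcomes section and the statistical sections, and in the registration if it carries the same wording (the record was not seen). The cost is that fMRI can no longer be reported as a stand-alone primary result.

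The change does not settle a separate matter: the abstract calls the trial non-inferiority, while the sample size is for a two-sided difference.

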#### Secondary outcomes

The Mini-Mental State Examination (MMSE) is widely used to assess the cognitive function in various clinical conditions, including post-stroke depression. This 30-point questionnaire evaluates domains such as orientation, attention, memory, language, and visuospatial abilities. A higher score indicates better cognitive function. In this study, MMSE will be used to evaluate cognitive status at baseline and after 12 weeks of intervention.

The modified Barthel index (MBI) is employed to evaluate the level of functional independence in activities of daily living (ADLs). The scale comprises 10 items, including feeding, bathing, grooming, dressing, and mobility. The scores range from 0 to 100, with higher scores reflecting greater independence. As PSD may negatively impact recovery in ADLs, the MBI serves as an essential secondary indicator of functional improvement.

The National Institutes of Health Stroke Scale (NIHSS) is a standardized tool used to quantify neurological deficits in stroke patients. It assesses multiple domains, including consciousness, motor strength, sensation, language, and visual fields. Scores range from 0 to 42, with higher scores indicating more severe deficits. Monitoring NIHSS scores provides insight into the interplay between PSD and the neurological recovery process.

Functional near-infrared spectroscopy (fNIRS) is conducted using two wavelengths of near-infrared light (690 nm and 830 nm) to measure oxygenated hemoglobin (oxy-Hb) based on the modified Beer–Lambert law. FNIRS assessments is performed at baseline, after 1 and 2 weeks of treatment. The study employed the Verbal Fluency Task (VFT) as a cognitive task to activate brain regions during fNIRS measurements, which is conducted on the same day as the tasks.

In this study, we selected IL-6, IL-4, IL-10, IL-17, TNF-*α*, interferon-*γ* (IFN-γ), adrenocorticotropic hormone (ACTH), and cortisol as key biomarkers to evaluate the interplay between inflammatory processes and hypothalamic–pituitary–adrenal (HPA) axis function in PSD. Pro-inflammatory cytokines such as IL-6, IL-17, TNF-α, and IFN-γ were measured to assess the level of systemic inflammation, which has been implicated in the pathophysiology of PSD. Anti-inflammatory cytokines, including IL-4 and IL-10, is evaluated to explore their potential regulatory effects. Additionally, ACTH and cortisol levels is used as indicators of HPA axis activation and stress response.

### Participant safety

When patients involved in this study, they will be required to understand the whole research plan, and sign the informed consent. In order to better prevention and treatment in this study may cause any damage, the researchers will detect any potential adverse events and truthfully recorded on the CRF table. In this study, adverse events is mainly related to treatment, including dizziness, headache, shortness of breath, palpitation. In the event of adverse events, will be in accordance with the contingency plans for processing. The investigator will first determine the severity of the adverse effects. Slight ae will by the doctor to treat. Serious ae report to the ethics committee will be made by the researchers.

### Quality control

This clinical study set up a quality inspector for the entire supervision. Test prior to the start of treatment of doctor training, unified specification operation, meet the requirements of technical specification rear can implement treatment. The relevant data collection will be completed between 8:00 a.m. and 16:00 a.m. A data monitoring committee, independent of the investigators, examined logic issues, ascertainment of values, processed abnormal safety indicators, missing values, compliance, standardization, completeness, and consistency throughout the study. The committee will be made by clinical physicians, statisticians, psychologist, and ethicist.

### Sample size calculation

The sample size for this study was calculated based on data from a previous clinical trial (20), in which the HAMD score was 9.90 ± 4.61 in the Tuina therapy group and 13.24 ± 4.36 in the conventional rehabilitation group. The combined standard deviation (*σ*) was 4.49. To detect a difference between group means (*Δ* = 2.5) with a statistical power of 80% (*β* = 0.2, corresponding to Zβ = 0.84) and a significance level of 0.05 (*α* = 0.05, corresponding to Zα/2 = 1.96), the required sample size per group was calculated using the following formula, with calculations performed in G*Power software to ensure adequate statistical power:

$$n=\frac{{\left(Z_{\alpha /2}+Z_{\beta }\right)}^{2}\cdot 2\sigma^{2}}{\Delta^{2}}$$

Thus, each group requires approximately 51 participants. Considering a 20% dropout rate, the adjusted sample size is 64. Therefore, a total of 64 participants per group will be required, resulting in a total sample size of 128 participants.

### Data collection and management

Two data managers who were not part of the study group and who were unaware of the group assignments were responsible for data entry and database establishment. All the related original data will be stored in Shuguang Hospital affiliated to Shanghai University of Traditional Chinese Medicine, and real-time uploaded to the Chinese clinical trial registry.

### Statistical analysis

#### Statistical analysis of scales and general information

All statistical analyses will be performed using SPSS version 26.0. Continuous variables will be presented as mean ± standard deviation (SD) and compared using independent t-tests or Mann–Whitney U tests based on data normality. Categorical variables will be expressed as frequencies and percentages and analyzed using chi-square or Fisher’s exact tests. Missing data will be handled using multiple imputation. To control for potential confounders, a multivariate regression analysis will be conducted. A two-tailed *p*-value < 0.05 will be considered statistically significant.

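### No single baseline-adjusted primary model is fixed for HAMD-17: the stated test is unadjusted, is chosen on a normality check, and sits beside an undefined regression

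*Protocol article*

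**What the plan says.** **Outcome.** The abstract (Methods and analysis) states: "The primary efficacy outcome is the change from baseline to week 2" in HAMD, with fMRI as a second primary outcome.

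**Sample size.** The section Sample size calculation rests on an earlier trial "in which the HAMD score was 9.90 ± 4.61 in the Tuina therapy group" and 13.24 ± 4.36 under conventional rehabilitation. These are group scores, and their time point is not stated. The combined SD is given as 4.49. With a difference of 2.5, 80% power and two-sided 0.05, the result is 51 per group, or 64 after 20% dropout.

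**Analysis.** The section Statistical analysis of scales and general information says that continuous variables are "compared using independent t-tests or Mann–Whitney U tests based on data normality". The primary outcome gets no rule of its own. Missing data are to be multiply imputed. Then: "To control for potential confounders, a multivariate regression analysis will be conducted". The outcome, the covariates and the standing of that regression are not given.

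**The concern.** Three things do not fit together: the outcome is a change, the power rests on the spread of a score, and the test is an unadjusted comparison picked after looking at the data.

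- **Choice of test.** Deciding between a t-test and a Mann-Whitney test on observed normality makes the primary analysis data-dependent. With the undefined regression there are three candidate results for one endpoint.
- **What is estimated.** The Mann-Whitney test does not estimate a difference in means, which is what the sample size is built on. It also yields no estimate and standard error of the kind that the usual rules for multiply imputed data combine.
- **Unused information.** Table 1 schedules HAMD-17 at week 0, yet no primary model is said to use it as a covariate.
- **Power.** The SD of a change differs from the SD of a score, so the stated 80% may not apply to a test of change.

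**Working it through.** **Inputs from the article:** SDs 4.61 and 4.36; difference 2.5; two-sided 0.05; 80% power; 51 evaluable per group; 20% dropout.

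**Assumed, because the article does not give them:** the correlation ρ between baseline and week-2 HAMD (a range is shown); 4.49 as the week-2 SD; and, in steps 2 and 3, the same SD at baseline.

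**Step 1. The article's own figure.**
- Pooled SD = √((4.61² + 4.36²)/2) = 4.49.
- n = (1.96 + 0.84)² × 2 × 4.49² / 2.5² = 50.6, so 51 per group.
- 51/0.8 = 63.75, so 64 per group and 128 in total. All three figures reproduce.
- Power at 51 per group with SD 4.49 is 79.5% (exact t) or 80.3% (normal approximation).

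**Step 2. Unadjusted t-test on change.** SD of change = 4.49 × √(2(1 − ρ)). This equals 4.49 at ρ = 0.5 and exceeds it below 0.5.

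**Step 3. ANCOVA on baseline.** Residual SD = 4.49 × √(1 − ρ²).

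| ρ | SD of change | Power, change | ANCOVA SD | Power, ANCOVA |
|---|---|---|---|---|
| 0.3 | 5.31 | 65.3% | 4.28 | 83.1% |
| 0.4 | 4.92 | 72.0% | 4.12 | 86.0% |
| 0.5 | 4.49 | 79.5% | 3.89 | 89.5% |
| 0.7 | 3.48 | 94.9% | 3.21 | 97.4% |

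(Exact noncentral t, 51 per arm. At ρ = 0 ANCOVA gives 79.5%, the same as the article's own design.)

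**Step 4. Why ANCOVA does not lose.** With baseline SD b and week-2 SD w, the variance of change is b² + w² − 2ρbw = (b − ρw)² + w²(1 − ρ²). The last term is the ANCOVA residual variance, and the first is never negative. Nor can w²(1 − ρ²) exceed w², the variance of the week-2 score. Apart from one degree of freedom, which is negligible here, ANCOVA is therefore no less powerful than either unadjusted analysis at any ρ.

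**Step 5. Sensitivity.**
- *Smaller baseline SD.* The change-score test breaks even with SD 4.49 at ρ = b/(2 × 4.49). For an assumed b of 3.5 that is 0.39, with power 74% at ρ = 0.3 and 80% at 0.4. For b = 3.0 it is 0.33, with 78% and 83%. The ANCOVA column does not depend on b.
- *No dropout (64 per arm, equal SDs).* Change-score power is 75% at ρ = 0.3 and 81% at 0.4.
- *Larger week-2 SD.* At SD 5.0, ANCOVA with 51 per arm gives 75% at ρ = 0.3 and 82% at 0.5; at SD 5.5, 66% and 75%.
- *Mann-Whitney branch on normal data.* With relative efficiency of about 0.955, power is about 78% where the t-test has 80% (normal approximation).

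**The case against.** An unadjusted t-test between randomised arms is valid, and the sample size reproduces. A condensed article may leave the covariate list to an analysis plan, and the regression could include baseline HAMD. The statistical section does not say that the t-test is run on change scores. If week-2 scores are compared, SD 4.49 is the right kind of SD and power is about 80% whatever ρ is. The entry range (HAMD-17 above 7 and up to 24) may lower ρ, but it would also tend to shrink the baseline SD, which works the other way.

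Most of this stands, and it rules out three stronger readings that a reader might draw.

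- *The plan has no baseline adjustment.* The regression neither names nor excludes baseline HAMD. What can be said is that no baseline-adjusted primary model is fixed.
- *The trial is underpowered.* The shortfall needs a change-score test, a ρ below break-even (0.5 only if the SDs are equal) and the full 20% dropout. The documents establish none of these.
- *ANCOVA guarantees 80%.* It does so only for a difference of 2.5, a week-2 SD of 4.49 and about 51 evaluable per arm. It gives no assurance for the non-inferiority objective named in the abstract, for which no margin is stated.

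The objection does not reach the data-driven choice of test. That is a rule the article states, not a detail left out, and it is a weak rule at any ρ.

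**Conclusion.** The point holds as a matter of analysis choice. The article fixes a primary comparison that is unadjusted and selected on the data, one branch of which does not estimate the quantity used for sizing and fits poorly with multiple imputation. A regression of undefined standing is added.

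The size of the power issue is conditional. On the change-score reading, with equal SDs and 51 per arm, power runs from about 65% at ρ = 0.3 to 95% at ρ = 0.7, against 83% to 97% for ANCOVA. The gain is about 18 percentage points at 0.3, 10 at 0.5 and 2 at 0.7. The sample size arithmetic is not in error. The change should be made because it improves the analysis at no cost in patients, not because the trial has been shown to fail its power target.

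**What to change.** - Make the single primary analysis of HAMD-17 an ANCOVA of the week-2 score on group and baseline HAMD-17, reporting the adjusted mean difference with its 95% CI.
- Use it whatever the normality check shows, with robust standard errors or a bootstrap if residuals are skewed, and pool it over the imputed data sets.
- Label rank tests and any other adjusted regression as sensitivity analyses.
- State in the sample size section that 4.49 is the SD of scores.

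The cost is wording only. Baseline HAMD-17 is already scheduled, and the named software (SPSS) fits the model. The non-inferiority label still has to be reconciled separately with a sample size built on a difference to detect.

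Suggested text: *The primary analysis of HAMD-17 compares week-2 scores between groups by analysis of covariance with baseline HAMD-17 as covariate, irrespective of tests of normality; results are pooled over imputations and given as an adjusted mean difference with 95% CI. Rank-based and other adjusted analyses are sensitivity analyses.*
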